## Abstract

**Background:**

Chronic low back pain (CLBP) is a persistent disabling condition with rising significant healthcare, social and economic costs. Current research supports the use of exercise-based treatment approaches that encourage people with CLBP to assume a physically active role in their recovery. While international clinical guidelines and systematic reviews for CLBP support supervised group exercise as an attractive first-line option for treating large numbers of CLBP patients at low cost, barriers to their delivery include space and time restrictions in healthcare settings and poor patient attendance. The European Clinical Guidelines have identified the need for research in the use of brief/minimal contact self-activation interventions that encourage participation in physical activity for CLBP. Walking may be an ideally suited form of individualized exercise prescription as it is easy to do, requires no special skills or facilities, and is achievable by virtually all ages with little risk of injury, but its effectiveness for LBP is unproven.

**Methods and design:**

This study will be an assessor-blinded randomized controlled trial that will investigate the difference in clinical effectiveness and costs of an individualized walking programme and a supervised general exercise programme compared to usual physiotherapy, which will act as the control group, in people with chronic low back pain. A sample of 246 patients will be recruited in Dublin, Ireland through acute general hospital outpatient physiotherapy departments that provide treatment for people with CLBP. Patients will be randomly allocated to one of the three groups in a concealed manner. The main outcomes will be functional disability, pain, quality of life, fear avoidance, back beliefs, physical activity, satisfaction and costs, which will be evaluated at baseline, and 3, 6 and 12 months [follow-up by pre-paid postage]. Qualitative telephone interviews and focus groups will be embedded in the research design to obtain feedback about participants' experiences of the interventions and trial participation, and to inform interpretation of the quantitative data. Planned analysis will be by intention to treat (quantitative data) and thematic analysis (qualitative data)

**Discussion:**

The trial will evaluate the effectiveness of a walking programme and a supervised general exercise programme compared to usual physiotherapy in people with CLBP.

**Trial registration:**

Current controlled trial ISRCTN17592092

## Background

Chronic low back pain (CLBP) is a persistent disabling condition with rising significant healthcare, social and economic costs [1,2]. Current research and both European and American Clinical Guidelines supports the use of exercise-based treatment approaches that encourage people with chronic low back pain (pain >3 months) to assume a physically active role in their recovery [3-6]. However, these patients often report decreased habitual physical activity levels, believing that if movement hurts they may be re-injuring themselves, termed 'fear avoidance'[7,8].

The recent European Clinical Guidelines for CLBP concluded that supervised group exercise is an attractive first-line option for treating large numbers of CLBP patients at low cost [6]. The "Back to Fitness" physiotherapy-led supervised group exercise programme for CLBP was introduced in the UK in the 1990s [9]. Its effectiveness has been supported in several RCTs, reporting significant improvements in pain and disability compared to 'routine' physiotherapy (i.e. advice/education, passive mobilisation/manipulation)[10] and GP management [11], and it has been shown to be cost effective[11]. Nonetheless, a national survey by the Principal Investigator of public general hospitals in the Republic of Ireland (ROI), found that only 39% of responding physiotherapy departments were delivering group-based exercise programmes for CLBP, the main barriers being space and time restrictions, and insufficient staffing levels [12].

Furthermore, another limiting factor from the patients' perspective is poor adherence with the recommended exercises [13], and the requirement for regular attendance at the class with drop out rates of up to 30% being reported in the literature [14]. Given the difficulties and limited availability of supervised exercise programmes, an alternative clinically and cost effective approach to increasing the activity levels of patients with CLBP is warranted.

The European Clinical Guidelines have identified the use of brief/minimal contact self-activation interventions that encourage participation in physical activity for CLBP as an area for future research, particularly as this approach could result in significant cost savings if it proves to be at least as effective as other treatments [6]. For CLBP, there is moderate evidence from RCTs [15,16] and a systematic review [3] that brief information and advice to stay active are more effective than usual GP care in reducing LBP-related disability, but not pain levels. However, there is limited evidence of the effects of self-activation interventions compared to supervised exercise programmes on pain and disability levels [17], and no evidence of the effects of either type of programme in increasing CLBP patients' level of participation in physical activities, return to work rates or psychosocial variables compared to 'routine' physiotherapy.

Walking may be an ideally suited form of exercise prescription as it is easy to do, requires no special skills or facilities, and is achievable by virtually all ages with little risk of injury [18,19]. General physical activity recommendations encourage individuals to accumulate 30 minutes of moderate intensity physical activity on five days per week [20] or 10,000 steps [21]; and there is evidence from a meta-analysis that healthy but sedentary individuals who take up a programme of regular brisk walking improve several known risk factors for cardiovascular disease [22]. There is limited evidence that people with LBP are less physically active and have altered patterns of physical activity than matched controls [23,24]. Several recent studies have reported that people with chronic LBP failed to reach the recommended 10,000 steps per day and took significantly less steps than healthy age-matched controls [24,25].

There has been minimal investigation of the effectiveness of walking programmes in LBP management. One RCT found unsupervised walking at a self-selected pace was less effective than individual physiotherapy or medical exercise therapy in reducing pain, disability, costs and increasing patient satisfaction levels in people with CLBP [26]. Participants in the walking group were instructed to walk for one hour three times per week at their convenience, preferably on alternate days. However, apart from one information session, participants in the walking group received no further contact or support from a health professional, and their level of compliance or physical activity was not investigated. From a North American study back pain sufferers who participated in brisk walking for at least 3 hours per week reported reductions in low back pain, disability, and psychological distress [27]. Nonetheless, that trial was primarily designed to compare chiropractic and medical care for LBP, and thus patients did not receive any structured physical activity or exercise interventions and no details of the walking intervention are provided. Given the limited research to support or refute walking programmes in CLBP management, there is a need to investigate the effectiveness of such programmes in people with chronic LBP.

For the researchers designing such walking programmes, and the clinicians delivering them, the challenge is to devise an effective intervention that will motivate habitually sedentary people with LBP to be physically active. A Cochrane systematic review of interventions to promote physical activity concluded that a mixture of self-direction and on-going professional support can encourage adults to be more physically active [28]. A randomised controlled trial found that an eight-week low frequency progressive walking programme for 'normal' sedentary adults had high levels of adherence, and resulted in increased physical activity levels with no adverse effects or injuries, thus increasing its clinical application [29]. Another trial reported evidence for the benefit to fitness and cardiovascular risk of the '30 minute brisk walking, five days per week' message to people aged 50–65 years who participated in a 12 week unsupervised home-based walking programme that used pedometers as motivational tools [30]. Pedometers are simple to use, inexpensive devices that produce a user-friendly output (step count, duration) that serves as an effective motivator to increase physical activity [31].

A self-activation programme by walking may be a more pragmatic and less costly intervention than supervised exercise classes to promote increased physical activity levels in patients with CLBP. It has the additional advantages of supporting a larger population of CLBP patients at the same time, and by moving the emphasis away from the hospital setting could reduce the costs to the Health Service. Given that the majority of patients with CLBP currently receive a range of interventions within the scope of 'usual' physiotherapy (advice, passive mobilization/manipulation, general exercise [32-34], this RCT will establish the difference in effectiveness of a walking programme and a supervised general exercise programme compared to usual physiotherapy, which will act as the control intervention, in subjects with chronic low back pain.

The *primary objective *is to:

(i) determine the difference between groups in mean change in functional disability at 6 months

The *secondary objectives *are to:

(ii) determine the difference between groups in mean changes in pain, health-related quality of life, psychosocial beliefs, days of sick leave, daily physical activity levels, self efficacy, readiness to change and patient satisfaction

(iii) determine the difference between groups in cost utility and the cost effectiveness of the alternative treatment programmes

(iv) determine the difference between groups in level of adherence to each intervention

(v) complete a qualitative exploration of subjects experience of each intervention

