### Hypotheses Tested

The trial will test two 'null' hypotheses. The primary null hypotheses is that,

(a). in people referred for physiotherapy for chronic LBP there is no difference in clinical outcome and costs between those receiving a walking programme, a supervised general exercise programme and usual physiotherapy;

The secondary null hypothesis is that:

(b). subjects that have received a walking programme or supervised general exercise programme will not have changed daily physical activity levels compared to those who have received usual physiotherapy

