## Methods/design

The Research Ethics Committees of the participating Dublin hospitals have granted approval for this study:

1. Adelaide and Meath Hospital incorporating the National Children's Hospital

2. Beaumont Hospital

3. Connolly Hospital

4. Mater Misericordiae University Hospital

5. St Vincent's University Hospital

The trial will be reported according to the recommendations of the CONSORT statement [35] and the flow of participants through the study is represented in Figure 1. The quantitative study will establish the difference in clinical effectiveness and costs of a walking programme and a supervised general exercise programme compared to usual physiotherapy, which will act as the control intervention, for patients with chronic low back pain. The qualitative study will explore participants' experience of the study and the interventions.

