### Quantitative study

#### Design

The study will be a prospective randomized controlled trial (RCT) with three arms (i) walking programme, (ii) a supervised exercise class, (iii) usual physiotherapy of up to 8 weeks duration. Outcomes will be assessed at baseline and 3, 6 and 12 months [follow-up by pre-paid postage].

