### Sample Size

A total of 189 patients (n = 63 per group) will be required for 80% power to detect a 4 point difference between groups on the primary outcome, the Oswestry Disability Index [39], with 95% confidence using a two-tail between-within repeated measures ANOVA test of difference between group means. Based on the results of previous LBP trials investigating exercise [11] and using postal follow-ups [40], we anticipate a 30% loss to follow-up. Thus we aim to recruit 82 subjects per group (total 246 subjects).

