### Clinical Outcomes

The **primary outcome measure **will be a change in:

(i) *Functional disability *due to LBP measured by the Oswestry Disability Index (ODI) [43]

The **secondary outcome measures **will be changes in:

(ii) *Pain *using Numerical Rating Scales for current and worst pain [44]

(iii) *Health-related quality of life *measured by the EuroQol questionnaire [45]

(iv) *Psycho-social beliefs *using the Fear Avoidance Beliefs Questionnaire [46] and the Back Beliefs Questionnaire [47]

(v) *Employment status and number of days reported sick leave over the past year *for those in paid employment only

(vi) *Self-report physical activity levels *using the International Physical Activity Questionnaire (IPAQ) [48],

(vii) *Objective physical activity levels *using an activPal™ device: a valid and reliable measure of walking that is capable of recording steps, time spent lying/sitting, standing and stepping under free living conditions [49] previously used by some of the authors in another LBP trial [50]. A sample of convenience of participants from each group will be requested to wear the activPAL™ on 3 separate occasions each lasting 7 days (1) at baseline, (2) 3 months and (3) 6 months after initial randomisation.

(viii) Self efficacy questionnaire [51]

(ix) Readiness to change questionnaire [52]

(x) *Patient satisfaction *will be assessed using Likert scales assessing satisfaction with outcome and satisfaction with care at 3 months [53]

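### The primary objective is ODI change at 6 months, but the primary null names neither ODI nor a time point and adds costs, and the planned ANOVA is tied neither to 6 months nor to the comparison with usual physiotherapy

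*Protocol article*

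**What the plan says.** The Background section sets the primary objective: "determine the difference between groups in mean change in functional disability at 6 months". The same section ranks costs as a secondary objective: "determine the difference between groups in cost utility and the cost effectiveness of the alternative treatment programmes". Clinical Outcomes names change in ODI as the only primary outcome and gives no visit.

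Hypotheses Tested states the primary null as: "there is no difference in clinical outcome and costs between those receiving a walking programme, a supervised general exercise programme and usual physiotherapy". It mentions neither ODI nor a time point.

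On the comparison of interest, Methods/design describes the two programmes as "compared to usual physiotherapy, which will act as the control intervention". The Abstract and Background say the same.

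On timing, Design says: "Outcomes will be assessed at baseline and 3, 6 and 12 months". On the test, Sample Size powers the trial for a 4-point ODI difference "using a two-tail between-within repeated measures ANOVA test of difference between group means". Data Analysis plans the same type of model for all continuous outcomes and speaks of differences from baseline at follow-up. Neither section says which F term decides, which visits enter, or whether 6 months has special standing.

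**The concern.** The objective, the null and the test should describe one comparison, and here they describe three. The objective is disability at one visit. The null is an unspecified clinical outcome together with costs, at no visit. The test is a model that, applied to the visit schedule, yields a group effect averaged over visits and a group-by-time effect sensitive to a difference at any visit. Neither term isolates 6 months, and neither compares a programme with usual physiotherapy.

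A short-lived effect is plausible. The interventions last up to 8 weeks, and Outcome Measures treats 3 months as the end of the scheduled intervention period. A benefit present at 3 months and gone by 6 could therefore yield a significant headline test although the primary objective was not met. Because the deciding term, visit and contrast are not fixed, they could also be chosen after the results are seen.

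**Working it through.** **The plan's own figure.** Sample Size gives 63 per group for 4 points, 80% power and two-sided 5%, but no SD and no within-patient correlation, so 63 cannot be reproduced from the stated inputs. For one pairwise comparison, n = 2(1.960 + 0.842)² SD² / 4². With SD 8 this is 2 × 7.849 × 64 / 16 = 62.8, that is 63. SD 8 is thus back-solved from 63. It is an assumption, not a check of the plan.

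**Set-up.** Three arms, n = 63 each; four visits (baseline, 3, 6, 12 months); SD 8 at each visit; equal correlation ρ between visits, 0.5 to 0.7; one arm differs by 4 points at a single follow-up visit. SD and ρ are assumed; the remaining figures are the protocol's.

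**Group-by-time term** (df 6 and 558). The interaction sum of squares for a single-cell shift is 4² × (1 − 1/3) × (1 − 1/4) = 8. The noncentrality is λ = 63 × 8 / [64(1 − ρ)].
- ρ = 0.5: λ = 504/32 = 15.75, power 0.86.
- ρ = 0.7: λ = 504/19.2 = 26.25, power 0.98.

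These values are the same whether the shift occurs at 3 months or at 6 months.

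**Group main effect, baseline included** (df 2 and 186). The shifted arm's mean over four visits moves by 1 point, so the between-arm sum of squares is 2/3, and λ = 63 × 4 × (2/3) / [64(1 + 3ρ)].
- ρ = 0.5: λ = 168/160 = 1.05, power 0.14.
- ρ = 0.7: λ = 168/198.4 = 0.85, power 0.12.

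**6-month change contrast, one programme against usual physiotherapy.** The SD of change is 8√[2(1 − ρ)], and SE = SD of change × √(2/63).
- ρ = 0.5: SD of change 8.00, SE 1.43, 4/SE = 2.81, power 0.80.
- ρ = 0.7: SD of change 6.20, SE 1.10, 4/SE = 3.62, power 0.95.

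A three-arm test of 6-month change has power 0.83 and 0.97 in the same two cases.

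| True effect in one arm | Group-by-time | Group main effect | 6-month contrast |
|---|---|---|---|
| 4 points at 3 months only | 0.86 to 0.98 | 0.12 to 0.14 | 0.05 |
| 4 points at 6 months only | 0.86 to 0.98 | 0.12 to 0.14 | 0.80 to 0.95 |

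**Wrong arm.** With a 4-point benefit of the class alone at all follow-ups (ρ = 0.5), the group main effect has power 0.79 and group-by-time 0.86. The 6-month contrast of walking with usual physiotherapy rejects in 5%. A significant ANOVA term does not say which programme differs from control.

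**Sensitivity.** Take ρ from 0.3 to 0.7, with either the visit SD or the SD of change set to 8. Group-by-time then rejects in 70 to 98% for the 3-month-only effect, and the group main effect has 9 to 22% power for the 6-month-only effect.

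**The case against.** The best reply is that the article does settle the essentials. The objective names disability at 6 months, Clinical Outcomes names ODI alone as primary, and Sample Size attaches the ANOVA to ODI. On this view the null is only loosely worded, and the model term and visit contrast are details that a condensed article leaves to the analysis plan. If only baseline and 6 months entered the model, group-by-time would be exactly the three-arm comparison of 6-month change. If change scores were analysed, no baseline level would be averaged in. The objective itself says between groups, so a three-arm test does not contradict that sentence.

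Much of this stands, and it rules out several stronger readings:
- A reader might infer that the primary test combines ODI with costs. It does not: costs appear in the null only, and Data Analysis handles them separately.
- A reader might infer that a real 6-month benefit would generally be missed. That applies mainly to the group main effect with baseline included; group-by-time has 86 to 98% power in the 6-month-only case.
- A reader might set the ANOVA against a baseline-adjusted 6-month analysis and credit the whole gain to the choice of visit. Part of that gain comes from the adjustment, so the fair comparator is the change-score contrast, at 80 to 95%.
- A reader might infer a family-wise error of 9 to 12% from unadjusted pairwise tests. The protocol plans no such tests, so this is not a property of it.

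The reply does not remove the disagreement between the objective and the null, which are both stated in this article. Nor does any sentence restrict the model to baseline and 6 months. An analysis plan could resolve the matter only by overriding one of the published statements.

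**Conclusion.** The concern holds in this form: the objective, the primary null and the planned test do not describe the same comparison. The mismatch between objective and null is certain from the text. So is the absence of any tie between the ANOVA and either 6 months or the control comparison. That all four visits enter the model is inferred from the schedule, the deciding term is not stated, and no explicit success rule is written.

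The size is therefore conditional on SD 8, correlation 0.5 to 0.7 and 63 per arm. The firmer risk is a positive headline without a 6-month effect: 86 to 98% for group-by-time against 5% for a 6-month contrast when the effect is confined to 3 months. The risk of missing a 6-month-only effect (12 to 14% power) arises only if the group main effect with baseline included decides.

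**What to change.** 1. Restate the primary null as no difference between arms in ODI change at 6 months, and take costs out of it.
2. Make the primary test the two 6-month contrasts from the repeated-measures model: walking against usual physiotherapy, and class against usual physiotherapy.
3. Gate both by a three-arm test at 6 months at 5%. With exactly three arms, each contrast can then be tested at 5% and the family-wise error stays at 5%: if all arms are equal the gate controls it, and if one arm differs from the other two, at most one pairwise null is still true.
4. Label the 3- and 12-month results, the other outcomes and costs as secondary.

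This needs no new data or visits, only rewording of the hypothesis, sample size and analysis sections. The all-visit ANOVA loses primary status. A contrast counts only if the gate also passes, so its power cannot exceed the smaller of the two: at SD 8 and correlation 0.5, at most 0.80 when one arm differs by 4 points.

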### Hypotheses Tested

The trial will test two 'null' hypotheses. The primary null hypotheses is that,

(a). in people referred for physiotherapy for chronic LBP there is no difference in clinical outcome and costs between those receiving a walking programme, a supervised general exercise programme and usual physiotherapy;

The secondary null hypothesis is that:

(b). subjects that have received a walking programme or supervised general exercise programme will not have changed daily physical activity levels compared to those who have received usual physiotherapy

## Methods/design

The Research Ethics Committees of the participating Dublin hospitals have granted approval for this study:

1. Adelaide and Meath Hospital incorporating the National Children's Hospital

2. Beaumont Hospital

3. Connolly Hospital

4. Mater Misericordiae University Hospital

5. St Vincent's University Hospital

The trial will be reported according to the recommendations of the CONSORT statement [35] and the flow of participants through the study is represented in Figure 1. The quantitative study will establish the difference in clinical effectiveness and costs of a walking programme and a supervised general exercise programme compared to usual physiotherapy, which will act as the control intervention, for patients with chronic low back pain. The qualitative study will explore participants' experience of the study and the interventions.

